**Methods:**

In this proposed multicenter, single-blinded, randomized controlled trial, 108 patients with mild-to-moderate plaque psoriasis will be randomly assigned to two groups in a 1:1 ratio to receive either internal or external TCM treatment, and 270 patients with severe plaque psoriasis will be randomly assigned to three groups in a 1:1:1 ratio to receive treatment with TCM or WM, or TCM + WM. All enrolled patients will receive 8 weeks of treatment. Follow-up assessments will be done 8 weeks after the treatment. The primary outcome of this study is the evaluation of efficacy and relapse rate, based on the Psoriasis Area and Severity Index, and the secondary outcome measures include determination of the affected body surface area, physician’s global assessment, pruritus scores (determined using a visual analog scale), TCM symptom score, Dermatology Life Quality Index, patient-reported quality of life score and incidence of serious adverse events.

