### Sample size

The sample size for this study was calculated based on the expected value of the efficacy based on the results from previous studies [17, 28]. The efficacy rates for groups A, B, C, D and E were 30.0%, 59.0%, 73.0%, 55% and 88.0%, respectively. The significance level (alpha) was set at 0.05 and the statistical power was 80%. Based on our calculation using the PASW statistical software (V.18.0), a sample size of 43 patients was required for groups A and B and 72 patients for groups C, D and E. However, considering a potential 25% loss of patients during follow-up, we adjusted the total sample sizes of groups A and B to 54 patients and that of groups C, D and E to 90 patients.

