### Assignment of interventions: allocation

#### Sequence generation

Eligible patients with mild-to-moderate or severe psoriasis will be enrolled at each of the six participating institutions and will be randomized separately. During their second visit, patients with mild-to-moderate psoriasis will be randomly assigned to either group A or group B in a 1:1 ratio, while those with severe psoriasis will be randomly assigned to group C, group D or group E in a 1:1:1 ratio. Randomization will be performed using a computer-generated random assignment sequence through the central layering and block randomization method of SAS software (V.9.4).

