### Statistical methods

All analyses will be performed by applying the SPSS V.21.0, (SPSS Inc., Chicago, IL, USA) statistical software and the data network platform designed by the data management center of Jiangsu Famaisheng Medical Technology. The outcome investigators will be blinded to group allocation. According to the principle of an intention-to-treat analysis, all patients who will be randomized and evaluated according to the efficacy indicators at least once are defined as the full analysis set population, whereas all patients who meet all inclusion and exclusion criteria and deviated from the prescribed dose less than 20% of the regimen are defined as the per-protocol set population. Patients who received treatment one or more times and have at least one safety evaluation will be analyzed in the safety set population. The efficacy measurement will be evaluated mainly by intention-to-treat analysis (full analysis set) and supplemented by per-protocol analysis. The safety evaluation will be analyzed in the safety set population.

If a numerical variable shows normal distribution and the variance is uniform, the statistical description will be expressed as the mean ± standard deviation; the statistical inference will be expressed by the F and S-N-K tests; and the repeated measurement of data analysis of variance will be used for comparison among the groups at multiple time points. In case a numerical variable shows skewed distribution, the median and minimum and maximum values will be used for statistical description; the rank sum test and Nemenyi test will be used for statistical inference, and the generalized estimation equation will be used for comparison among the groups at multiple time points. For categorical variables, the frequency, constituent ratio and rate will be used for statistical description. If the analysis index is unordered, a chi-squared test will be used for statistical inference and, if the analysis index is ordinal, a nonparametric test will be used for statistical inference. The generalized estimation equation will be used for comparison among the groups at multiple time points. Hypothesis testing will be performed using a two-sided test with 95% confidence intervals. A *P* value less than 0.05 indicates statistical significance.

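### For skewed outcomes compared at one time point among groups C, D and E, the single-step Nemenyi test is valid but gives up power that a closed rank procedure would keep at the same 5% family-wise error

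*Protocol article*

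**What the plan says.** The Statistical methods section chooses the method by the distribution of the variable. For normal data with equal variances, "the statistical inference will be expressed by the F and S-N-K tests", so pairs are followed up with a stepwise procedure. For skewed data the summary is the median with the range, and "the rank sum test and Nemenyi test will be used for statistical inference". The same sentence then assigns comparisons over several time points to generalized estimating equations (GEE). Tests are two-sided at 0.05.

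Pairwise follow-up is needed only where there are more than two arms. Under Sequence generation, "those with severe psoriasis will be randomly assigned to group C, group D or group E in a 1:1:1 ratio"; the mild-to-moderate cohort has only groups A and B. The Sample size section plans 72 per group for C, D and E, raised to 90 for losses, from binary efficacy rates of 73%, 55% and 88%. It gives no effect size or standard deviation for any numerical outcome.

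**The concern.** Nemenyi ranks all three arms together and holds every pair to one critical value, large enough to protect all three comparisons at once. With three arms that protection is not needed once the overall rank test is significant, as shown under the working. The cost falls on numerical outcomes that may be skewed and are compared among C, D and E at one visit: PASI score, BSA, pruritus VAS, TCM symptom score and DLQI.

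Two features make the choice look unplanned. First, the normal-data branch of the same paragraph already uses a stepwise test, so the power for an outcome shifts with the branch it falls into, and no reason is given. Second, under joint ranking the verdict on C v D depends on the data of E. The further E lies from the other two, the more the ranks of C and D are squeezed together and the weaker that comparison becomes.

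**Working it through.** **Plan's own figure.** There is none to reproduce: the protocol states no power for a numerical outcome. Its 72 and 90 per arm are used below only as group sizes (90 = 72 × 1.25).

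**Why the closed procedure keeps 5%.** With three groups, any two pairwise null hypotheses together imply that all three groups are equal. The closed family therefore has four members: the overall hypothesis and the three pairs. A pair is declared different only if the overall test and that pair's own test both reject at 0.05.
- All three arms equal: a false claim needs the overall test to reject, probability about 5%.
- Exactly one pair equal: a false claim needs that pair's rank sum test to reject, probability about 5%.
- Exactly two pairs equal is impossible.

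**Critical values.** The closed procedure uses z = 1.960 for each pair. Nemenyi uses one of two values, and the protocol does not say which form is meant.
- Studentized-range (Tukey) form: q(0.95; 3, ∞)/√2 = 2.344, pairwise P = 0.0191.
- Chi-squared form: √χ²(0.95; 2) = 2.448, pairwise P = 0.0144.

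Take a pair with 80% power at z = 1.960. Its expected z is 1.960 + 0.842 = 2.802.
- Tukey form: Φ(2.802 − 2.344) = Φ(0.458) = 67.6%, a loss of 12.4 points.
- Chi-squared form: Φ(2.802 − 2.448) = Φ(0.354) = 63.8%, a loss of 16.2 points.

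This reflects the critical value alone. Joint ranking can add to the loss, and the overall test required by the closed procedure can reduce it, so simulation is needed.

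**Simulated power (%).** Pure location shift, at least 4,000 runs per row (Monte Carlo standard error at most √(0.25/4000) = 0.8 points). Rank tests do not change under a monotone transformation, so these rows also cover log-normal data shifted on the log scale. Shifts are in SD on the normal scale. Losses are in points, Tukey form / chi-squared form, and approximate because the powers are rounded.

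| Per arm | Shifts | Pair | Nemenyi, Tukey | Nemenyi, chi-squared | Closed | Loss |
|---|---|---|---|---|---|---|
| 72 | 0, 0, 0.5 | each differing pair | 71 | 67 | 79 | 8 / 12 |
| 72 | 0, 0.25, 0.5 | neighbouring | 18 | 15 | 29 | 11 / 14 |
| 72 | 0, 0.25, 0.5 | widest | 72 | 68 | 73 | 1–2 / 5 |
| 72 | 0, 0.4, 0.8 | neighbouring | 46 | 42 | 64 | 18 / 22 |
| 90 | 0, 0.43, 0.86 | neighbouring | 64–65 | 60–61 | 80 | 15–16 / 19–20 |
| 90 | 0, 0.43, 0.86 | widest | 100 | 100 | 100 | 0 / 0 |
| 90 | 0, 0.215, 0.43 | neighbouring | 16–17 | 14 | 27 | 10–11 / 13 |

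The gap is similar at the two sizes but absolute power is not. With 0.43 SD between neighbours, the figures at 72 per arm are 53–54% (Tukey form) v 71% (closed).

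**Ordering as in the sample size section.** Purely as an illustration, turn 73%, 55% and 88% into probit shifts with 72 per arm. Power in the order Tukey / chi-squared / closed is then C v D 64 / 60 / 81, C v E 79 / 76 / 91 and D v E 100 / 100 / 100.

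**Error rates.**
- All arms equal, family-wise error: closed 4.8%, Nemenyi 4.8% (Tukey) or 3.7% (chi-squared).
- Two arms equal and the third moderately different, false-positive rate for the equal pair: closed about 5%, Nemenyi about 1–2%. With the third arm very far away, Nemenyi falls to 0.2–0.3%.

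**Wider grid.** Over shifts up to 1.2 SD, restricted to pairs where the closed test has 20–99% power, the loss runs from about 0 to 23 points (Tukey, median 9–10) or 0 to 28 points (chi-squared, median 12–14). The largest losses arise for a neighbouring pair when the third arm lies far away.

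**The case against.** Nemenyi is a recognised follow-up to the Kruskal-Wallis test, controls the family-wise error and errs on the safe side. Naming it states nothing wrong, and pairing a stepwise test for normal data with a single-step test for skewed data is a difference in efficiency, not a contradiction. This stands, and it is why the point is graded as an improvement.

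The scope is also narrow. The outcomes concerned are measured repeatedly, and the sentence that names Nemenyi sends comparisons over several visits to GEE. What remains is the comparison at a single time point. The sample size rests on binary efficacy rates, to which the Nemenyi sentence does not apply. Both limits stand.

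A reader might go further and infer that every pair among C, D and E loses power, or that the loss can be stated as a fixed band of points per pair. The documents support neither. A widely separated pair, as D v E may be, loses essentially nothing. The protocol supplies no effect size for a numerical outcome and does not say which form of Nemenyi is meant. A reader might also infer a type I error problem or a threat to the powered comparison; neither follows.

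The alternative has small costs of its own. Re-ranking each pair separately gives no simultaneous confidence intervals, and in rare cases the pairwise results may be non-transitive.

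**Conclusion.** The point holds as one of efficiency. For a skewed numerical outcome compared among C, D and E at one visit, the named test uses a critical z of 2.34 or 2.45 where 1.96 after a significant overall test would give the same 5% family-wise error. In the scenarios examined, the power given up is about 0 for a widely separated pair, about 8 points (Tukey form) where two arms coincide and the third differs, and about 10 to 18 points for neighbouring pairs. For neighbouring pairs in the chi-squared form it can reach 20 points or more. These figures assume a pure location shift and 72 to 90 analysed patients per arm. They are illustrations and not predictions for this trial. Grade: optional, cheap improvement.

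**What to change.** In the Statistical methods section, replace the rank sum and Nemenyi wording for skewed numerical variables at a single time point with text along these lines:

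*Groups C, D and E will be compared with the Kruskal-Wallis test at two-sided 0.05. If it is significant, each pair will be compared with a two-sample rank sum test, ranking that pair only, at two-sided 0.05 (closed testing for three groups). Groups A and B will be compared with the two-sample rank sum test alone.*

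Leave the GEE wording for several time points as it is. If confidence intervals are reported for the pairs, label them as not simultaneous. The cost is one short change of wording, best made before unblinding. It needs no further patients or data, and the 5% family-wise error is unchanged. If the sponsor prefers to keep Nemenyi, it would be enough to say which form is meant and to accept the lower power knowingly.

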## Abstract

**Background:**

Plaque psoriasis is a refractory inflammatory skin disease. The common therapies used to treat plaque psoriasis in traditional Chinese medicine (TCM) and western medicine (WM) have distinct characteristics and advantages. Although a combination of TCM and WM therapies, adjusted to the clinical situation, is widely used, there are no systematic studies on the hierarchical selection of this treatment combination based on the severity of skin lesions. We therefore designed a randomized clinical trial to focus on the sequence of internal and external treatments of TCM in patients with mild-to-moderate plaque psoriasis and to optimize the integration of Chinese and western medicine for the treatment of patients with severe plaque psoriasis, thereby achieving high-level clinical evidence and establish treatment norms for the integrated use of Chinese and western medicines.

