### Objectives

Although TCM and WM are both commonly used in the treatment of psoriasis and each has its own associated advantages and characteristics, the combined application of these two approaches can enhance the curative effect and reduce the side effects and recurrence rate of psoriasis. Therefore, the combination of TCM and WM therapies, adjusted according to the clinical situation, has been used widely in medical practice. However, there have been no previous clinical studies examining the hierarchical selection of treatment combinations according to the severity of skin lesions. To date, only the pairwise combinations of Chinese herbal medicine, cupping therapy and NB-UVB phototherapy for plaque psoriasis have been reported, and the curative effects were found to vary. Therefore, in this multicenter, randomized controlled, single-blind clinical trial, “Our Choice”, we combined JY granules (JYG) and moving cupping therapy for the treatment of mild-to-moderate plaque psoriasis, while for severe psoriasis we combined JYG, moving cupping therapy and NB-UVB phototherapy. This study aimed to optimize the internal and external TCM treatments and establish a high level of clinical evidence and treatment norms for the integration of Chinese and western medicines.

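### For response rates in the three-arm severe cohort the plan names a chi-squared test but no E v C or E v D comparison, so a significant result would not show that the combination beats its components

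*Protocol article*

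**What the plan says.** Statistical methods in the protocol article sets the test by type of data. Normally distributed numerical outcomes get an F test with S-N-K comparisons; skewed ones get a rank sum test with Nemenyi comparisons. For categorical outcomes it says "If the analysis index is unordered, a chi-squared test will be used for statistical inference", a nonparametric test if the outcome is ordinal, and generalized estimating equations for groups compared over several time points. No contrast between particular groups is given for any of these categorical methods. "Hypothesis testing will be performed using a two-sided test with 95% confidence intervals", and a P "value less than 0.05 indicates statistical significance".

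Sample size plans on rates: "The efficacy rates for groups A, B, C, D and E were 30.0%, 59.0%, 73.0%, 55% and 88.0%, respectively". From these, "a sample size of 43 patients was required for groups A and B and 72 patients for groups C, D and E", raised to 90 per group in the severe cohort for loss to follow-up.

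The Abstract gives the purpose of the severe cohort as "to optimize the integration of Chinese and western medicine for the treatment of patients with severe plaque psoriasis", with treatment norms to follow. The Objectives section starts from the premise that "the combined application of these two approaches can enhance the curative effect and reduce the side effects and recurrence rate of psoriasis".

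**The concern.** To support norms for integrated treatment, the severe cohort has to show what E achieves against C and against D. A chi-squared test on the 3 x 2 table asks only whether the three rates are all equal. It can be significant because WM alone does worse, while the combination adds nothing to TCM alone.

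The planning rates make this more than a theoretical worry, since C and D are themselves expected to differ by 73 - 55 = 18 percentage points. The plan supplies the step from overall test to group comparison for numerical outcomes and leaves it out for rates, which is the type of outcome on which the trial is sized. The harder contrast, E v C, would then sit behind an overall test that looks very well powered.

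This is distinct from multiplicity. It arises when the groups truly differ, and lowering alpha does not turn a test of C = D = E into a test of E against C.

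**Working it through.** **Inputs.** Rates C 73%, D 55%, E 88%; 80% power; 72 evaluable and 90 randomized per group (Sample size). Two-sided tests at 0.05 (Statistical methods). The values of D other than 55%, and E = C, are assumptions made to show a range.

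**The plan's own figure.** The 72 per group is not reproduced. For C v E with the pooled two-proportion formula, the mean rate is 0.805 and

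n = [1.96 × √(2 × 0.805 × 0.195) + 0.842 × √(0.73 × 0.27 + 0.88 × 0.12)]² / 0.15² = (1.098 + 0.463)² / 0.0225, which rounds up to 109.

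The same formula gives 111 for C v D and 29 for D v E. The three-group chi-squared test needs 36. That mismatch is a separate matter; 72 is used below only as the stated number evaluable.

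**Overall test when the combination adds nothing to TCM (C = E = 73%).** The approximate power is the chance that a noncentral chi-squared variable with 2 df exceeds 5.991, with noncentrality λ = n × Σ(pᵢ - p̄)² / [p̄(1 - p̄)].

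For D = 55% and n = 72: p̄ = 0.67; Σ(pᵢ - p̄)² = 0.06² + 0.12² + 0.06² = 0.0216; λ = 72 × 0.0216 / (0.67 × 0.33) = 7.03; power 65.8%. A simulation of 1,000,000 trials gives 65.6%.

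Simulated results, 72 per group, C = E = 73%:

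| D | Overall test significant | Overall significant and E at least level with both C and D |
|---|---|---|
| 55% | 66% | 35% |
| 60% | 39% | 21% |
| 65% | 18% | 9% |
| 73% | 5% | 2% |

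At D = 55% the overall figure is 76% with 90 per group and 62% with 67 per group (90 less 25%). In the same scenario with 72 per group, E is significantly better than C in 2.6% of trials, and better than both C and D in 2.5%.

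**At the plan's own rates (73/55/88%).** Here λ = 72 × (0.01² + 0.17² + 0.16²) / (0.72 × 0.28) = 72 × 0.0546 / 0.2016 = 19.5. Each pairwise result below is a two-sided chi-squared test at 0.05 with the difference in favour of E.

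| | 72 per group | 90 per group |
|---|---|---|
| Overall test significant (simulation) | 98.9% | 99.8% |
| E better than C | 63.9% | 72.8% |
| E better than both C and D | 63.8% | 72.8% |

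So even if the planning rates are true, about 35% of trials (98.9 - 63.8) with 72 per group would have a significant overall test without E being significantly better than both components. E v C decides almost everything.

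**The case against.** The sentence on the chi-squared test is a general rule for all categorical outcomes, including the two-arm A v B comparison. It does not say that C, D and E go into one table. If the test is run by pairs, the overall percentages above do not apply. Estimating equations are also named for rates over time, and confidence intervals are promised. The primary outcome is described as efficacy and relapse based on PASI, without a responder cut-off; if PASI were analysed as a score, S-N-K or Nemenyi would supply group comparisons. The analysis plan, not shown here, may name the contrasts.

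Much of this stands, and it limits the point to unordered rates and makes the percentages conditional on a three-group test. It does not remove the point. The article does fix a test for rates and adds group comparisons only for numerical data, while Sample size plans on rates. The estimating equations come with no contrast either. With pairwise tests, an E v D success is a correct result about E v D, but nothing says which pairs must succeed before the combination is called better.

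A reader might infer that the plan gives a false-positive rate of about 65%. It does not. With D at 55% and C and E at 73% the rates differ, so rejecting C = D = E is right; the figure falls quickly as D approaches C; and E also leads or ties in only 35% of trials. A reader might add the case E = D = 55%, C = 73%, where the overall test is significant in about 64% of trials. There E leads or ties with a significant test in only 0.2%, so it would hardly ever be mistaken for support of the combination.

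**Conclusion.** The point holds in a limited form. For unordered rates in the severe cohort, the named methods do not identify the comparisons that a conclusion about integrated treatment needs. If the chi-squared test is run across C, D and E, a significant result does not show that E is better than C or than D. How often that would arise with E = C depends on D: about 66%, 39% or 18% of trials at D = 55%, 60% or 65%, with C = E = 73% and 72 evaluable per group. At the planning rates, overall power of about 99% stands against about 64% for E beating both components (73% with 90 per group).

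The document nowhere says that a significant overall test will be taken as proof that the combination is superior, and the requirement that E beat both is drawn from the stated purpose rather than from a written hypothesis. What can be said is that the method as written cannot answer the question, not that a wrong claim has been planned.

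**What to change.** In Statistical methods, state that the severe-cohort conclusion on rates rests on two comparisons, E v C and E v D, each tested at two-sided 0.05 and reported as a rate difference with a 95% confidence interval. Conclude that the combination is superior to its components only if both favour E. Because both must succeed, this joint claim needs no split of alpha. If only E v D is met, conclude only that adding TCM to NB-UVB helps. Keep the three-group chi-squared test as descriptive, and give any estimating-equation analysis of rates the same two contrasts.

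The cost is a change of wording and two comparisons on data already being collected. The downside is that power for the combination claim is visibly lower than that of the overall test: about 64% at 72 per group and 73% at 90, under the plan's own rates.

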### Outcomes

#### Primary outcome

The primary outcome in this trial is evaluation of the efficacy and incidence of relapse in response to sequential treatment with integrated Chinese and western medicines during the treatment and follow-up periods. Relapse is defined as a PASI score exceeding the baseline score at the time of enrollment or development of new pustules or erythroderma [27]. PASI will be assessed at baseline, at 2-week intervals during the treatment period, and at 4-week intervals throughout the follow-up period.

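### Relapse incidence to week 16, if compared by the general chi-squared rule in a set needing one efficacy evaluation, ignores unequal observation time despite 25% expected loss

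*Protocol article*

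**What the plan says.** Under Primary outcome, the protocol article names "evaluation of the efficacy and incidence of relapse in response to sequential treatment" over both the treatment and the follow-up period. The event is fixed as follows: "Relapse is defined as a PASI score exceeding the baseline score at the time of enrollment or development of new pustules or erythroderma". The visit schedule is also fixed: "PASI will be assessed at baseline, at 2-week intervals during the treatment period, and at 4-week intervals throughout the follow-up period". The abstract adds "Follow-up assessments will be done 8 weeks after the treatment". With 8 weeks of treatment, PASI is therefore read at weeks 0, 2, 4, 6, 8, 12 and 16.

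Under Statistical methods, the main efficacy population is defined thus: "all patients who will be randomized and evaluated according to the efficacy indicators at least once are defined as the full analysis set population". Categorical variables are described by frequencies and rates, and the general rule for testing is "If the analysis index is unordered, a chi-squared test will be used for statistical inference". Generalized estimating equations are named for comparing groups across several time points. No time-to-event or censoring method appears.

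Under Sample size, the group sizes are raised "considering a potential 25% loss of patients during follow-up", from 43 to 54 in groups A and B and from 72 to 90 in groups C, D and E.

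**The concern.** Relapse is an event that can be seen only while a patient is still attending. A simple proportion of relapsed patients, compared by chi-squared, is a fair comparison of 16-week risk only if the groups were observed for comparable lengths of time. The plan itself expects a quarter of patients to be lost.

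A single efficacy evaluation, for example at week 2, puts a patient in the main analysis set. If that patient then stops attending, the plain incidence keeps him or her in the denominator with no opportunity to show a relapse at week 12 or 16. The analysis then measures who was seen to relapse, not who relapsed by week 16. Removing such patients instead would leave a completers' analysis, which is not the set that the article defines.

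This touches part of the primary outcome. Equal loss pulls differences toward zero. Unequal loss favours whichever group loses more patients.

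**Working it through.** The article gives no relapse rate, relapse difference or power for relapse, so there is no planned relapse figure to reproduce. The one stated figure that bears on the point is the allowance for loss.

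**Allowance for loss.** 43 × 1.25 = 53.75, rounded up to 54, and 72 × 1.25 = 90, so both inflated sizes reproduce as a 25% addition. The loss these sizes can absorb is 1 − 43/54 = 20.4% and 1 − 72/90 = 20.0%. I therefore use 20% to 25% as the range of loss.

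**Equal loss.** Let p be the true probability of relapse by week 16, L the share lost, and f the share of lost patients' relapses already recorded before they left. Assume that loss is unrelated to relapse. A plain incidence then has the expected value

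observed = p × [1 − L(1 − f)].

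With the same L and f in each group, the difference shrinks by L(1 − f), whatever p is:

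- L = 20%, f = 0: 20%
- L = 20%, f = 0.5: 10%
- L = 25%, f = 0: 25%
- L = 25%, f = 0.25: 18.75%
- L = 25%, f = 0.5: 12.5%

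**One timing scenario (assumed).** Spread 25% loss evenly over 16 weeks and split relapses equally between weeks 12 and 16. Then 0.25 × 12/16 = 18.75% are gone before week 12 and 25% before week 16. The shrinkage is 1 − (0.5 × 0.8125 + 0.5 × 0.75) = 21.9%. Patients lost before a first evaluation at week 2 (0.25 × 2/16 = 3.1%) leave the analysis set. Allowing for this gives 1 − 0.78125/0.96875 = 19.4%.

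**Unequal loss.** Assume true relapse of 40% v 20% (20 points) and f = 0:

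- Loss 30% v 20%: 0.40 × 0.70 − 0.20 × 0.80 = 12 points (40% too small)
- Loss 20% v 30%: 0.40 × 0.80 − 0.20 × 0.70 = 18 points (10% too small)
- Loss 10% v 30%: 0.40 × 0.90 − 0.20 × 0.70 = 22 points (10% too large)

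Now assume the same true relapse of 30% in both groups, with loss of 15% v 35%. The observed rates are 0.30 × 0.85 = 25.5% and 0.30 × 0.65 = 19.5%. This is a 6-point difference where none exists, and it favours the group that lost more patients.

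**What an analysis by observed time does.** In that last example, letting patients count only while seen gives 0.255/0.85 = 30% and 0.195/0.65 = 30%, so the false difference disappears when loss is uninformative. Counting all lost patients as relapsed gives 25.5% + 15% = 40.5% and 19.5% + 35% = 54.5%. The two extreme conventions therefore span 25.5–40.5% and 19.5–54.5%, which shows how far the comparison depends on patients not seen.

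**The case against.** The strongest reply is that the article contains no rule scoring lost patients as relapse-free. A reader might infer one from the chi-squared sentence and the analysis set, but nothing of the kind is written: no imputation, exclusion or censoring rule for relapse is given. The chi-squared sentence is general and does not name relapse. Rules for missing outcomes are commonly left to an analysis plan, which is not shown here, so that silence is not itself a fault. All of this stands, and it makes the point conditional. What remains is that the test and analysis set the article does choose are poorly suited to an incompletely observed event.

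A second reply is that generalized estimating equations are also named and would use only visits that took place. That is a fair reading for visit-by-visit comparisons. Such a model compares the proportion above baseline PASI at each visit, however, which is not the cumulative incidence named as the outcome, and the article does not assign it to relapse.

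Third, the consent section requires a final efficacy and safety evaluation from patients who decide to withdraw, and relapse can be recorded from week 2 because the definition needs no prior response. This stands in part. Some relapses of lost patients will be seen, which is why f appears above. The exit evaluation shows status at exit only, and it is written for patients who decide to withdraw, not for those who simply stop attending.

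A reader might also infer a fixed shrinkage of about a fifth, or charge the whole fall in power to the chi-squared test. The documents support neither. The size depends on assumed loss and timing. Most of any fall in power comes from the missing data, which no analysis restores, so no power figure is claimed here.

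**Conclusion.** The point holds in conditional form. The chosen test and analysis set do not account for differing observation time in part of the primary outcome, although substantial loss is expected. If a plain incidence is computed in the full analysis set, the attenuation under equal loss is at most 20–25%, and 10–12.5% if half of the lost patients' relapses were recorded first. Under unequal loss, neither the direction nor the size can be fixed in advance. These results rest on assumed relapse rates, relapse timing and loss patterns. The article supplies only the 25% loss figure and the visit schedule. This is an inexpensive improvement to the analysis, not a demonstrated bias in a written rule.

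**What to change.** In Statistical methods, name the relapse analysis separately from the general categorical rule. Analyse relapse as grouped (discrete-time) time to first relapse over the scheduled PASI visits, for example with a discrete-time complementary log-log model by group. Each patient contributes up to the last PASI visit attended. Report the week-16 relapse probability per group with its 95% confidence interval. Add a sensitivity analysis in which patients lost before week 16 are counted as relapsed.

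If the sponsor prefers to keep chi-squared, state before unblinding how patients without a week-12 or week-16 PASI are classified.

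The cost is wording and slightly more programming, with no new visits or data. Relapse is then reported as an estimated probability instead of a raw percentage. The main analysis assumes that loss is unrelated to relapse within each group. The sensitivity analysis probes that assumption but, as an extreme convention, does not correct for its failure.
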